### Power analysis and sample size calculation

Based on our findings from the Kids-HD sample, our central hypothesis is that GE participants will demonstrate altered trajectories in general brain size and cognition across YTO. Specifically, we predicted that GE individuals will demonstrate significantly larger brain volume (primary outcome measure) and stronger cognition scores (secondary outcome measures) prior to 20 YTO and significantly smaller brain volume and weaker cognition between 20−0 YTO. Using our updated recruitment target of 1,030 assessments across 450 participants, we estimated at least 90% power to reproduce our previous findings at p = .01 (except for cortical thickness; Table 5). Note that Table 5, which shows the results of our power analysis, includes functional and structural measures, but that our power analysis is primarily based on the structural findings from Kids-HD. Assuming 40% of participants are GE (as in the previous study), we can assume at least 400 visits from 180 unique genetically affected participants. The power analysis used the Kids-HD sample from Neema et al. (2024), and was based on 136 visits from 79 gene-expanded participants. Because the mean number of visits (and hence, statistical information) per participant will be higher in ChANGE-HD, a conservative estimate of the overall increase in statistical information (i.e., log-likelihood statistics) is obtained from the ratio of unique participants, which is 2.278. If the findings from Kids-HD hold, then the expected values of the analogous F statistics (Table 5) will increase by at least 2.278-fold. Standard power calculations using these projected F statistics yield results that exceed the above-claimed minimum statistical power.

**Table 5 pone.0336088.t005:** Tests used for hypotheses and power analysis (from Neema et al., 2024).

		Kids-HD				Change-HD		
**Measures**	**N**	**ndf**	**ddf**	**F**	**p**	**Projected F**	**Projected NCP**	**Power**
General Ability Index**	136	1	87.66	13.50	<0.001	30.78	29.445	0.997
Behavior composite**	135	2	120.27	10.91	<0.001	24.87	47.343	>0.999
PANESS**	128	1	46.12	8.92	0.005	20.34	18.933	0.956
Whole brain*	117	3	62.63	7.79	<0.001	17.76	49.491	>0.999
Cerebrum	117	3	62.55	7.80	<0.001	17.78	49.557	>0.999
Cortical gray matter*	117	1	99.90	12.22	<0.001	27.86	26.593	0.995
Cortical surface area	117	1	95.22	12.17	<0.001	27.75	26.468	0.994
Cortical thickness*	117	1	54.67	2.95	0.091	6.73	5.612	0.406

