$$\begin{array}{c} Age\;of\;motor\;symptom\;onset=\text{2}\text{1}.\text{5}\text{4}-(\text{9}.\text{5}\text{5}\text{6}-\text{0}.\text{1}\text{4}\text{6}*CAG) \end{array}$$

YTO is then calculated by simply subtracting participants’ ages (in years) from age of motor symptom onset. (The abbreviation YTO, now established by precedent, stands for a slight misnomer. The value is the number of years from the mean age of onset for those with the given CAG length. It is not the individual’s number of years to onset—which is unknowable—and is slightly different from the individual’s expected years to onset, given that they have reached their current age without already experiencing onset.)

A limitation of this YTO approach is that it can only approximate the relationship between true years to HD onset and the outcome measures. As noted earlier, the YTO calculations are slightly biased estimates of participants’ expected years to onset. Furthermore, a person’s true years to onset has a probability distribution around the CAG-specific average. For concave relationships, such as those we typically expect in the neurodevelopment of brain volumes, substitution of an average value for a probability distribution causes at least slight underestimation of the predicted value that would be obtained from a model based on the true (but unknowable) number of years from onset (Jensen’s inequality).

We assess the relationship between YTO and age- and sex-adjusted outcome measures in GE individuals using an additional mixed effects regression, again including random effects for repeated measures of the same participant and for similarities between participants from the same family. Similar to the GNE model described above, the potentially nonlinear influence of YTO is modeled using restricted cubic splines with degrees-of-freedom chosen by AIC. Sex and sex interactions with YTO are tested and included in the model if significant. The mixed effect models are fitted by maximum likelihood and F-test degrees of freedom are estimated using the Satterthwaite approximation. The summary of the resulting model indicates a p-value for the effect of YTO, which, if significant, indicates a statistically meaningful difference of GE from GNE along the YTO trajectory. Finally, we plot these relationships and their 95% confidence intervals to determine where these differences occur along the trajectory (50−0 YTO)

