To assess the relationship between age- and sex-adjusted neuroimaging variables (e.g., cortical grey and white matter volume, striatal volume, corticostriatal structural and functional connectivity, etc.) and clinical outcomes in GE individuals, we apply modeling techniques as described above. The models include random effects of subject and family, but exclude age and sex, as the values will have already been corrected using the data from GNE participants. Imaging measures are generally predictor variables, and clinical measures are the outcomes, reflecting the potential causal relationships between the two measurement classes. As in our previous work [17], we also split our GE participants into two groups with a cutoff of 20 YTO and test for differences in the imaging versus clinical relationships. This is based empirically on our work [17] showing divergence in neural and behavioral measures at this point in the YTO trajectory and because of work showing an upward trend in NfL at 20 YTO [18]. As described above, potential non-linear relationships between biomarkers and clinical measures are interrogated using restricted cubic splines (up to five degrees of freedom). For all analyses, a *p* value of < 0.05 is considered statistically significant.

In addition to our hypothesis-driven analyses, we also plan to perform detailed exploratory analyses to uncover novel neuroimaging biomarkers that both distinguish GE and GNE individuals and individuals with variations in HD-related single nucleotide polymorphisms (SNPs). For example, machine learning approaches, such as deep learning, have been applied to neuroimaging data from patients with neurodegenerative disorders to identify how those SNPs affect brain anatomy and function [81]. As mentioned above, SNPs in several genes explain variation in the eventual onset of motor symptoms in HD [32–34]. Using deep learning and other machine learning approaches as exploratory tools may reveal new mechanistic information about how these SNPs shape neurodevelopment and -degeneration.

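### The imaging-clinical models in gene-expanded participants state no YTO term, so shared disease stage alone can produce significant brain-behaviour associations well above the nominal 5%

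*Protocol article*

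**What the plan says.** All of this is in the protocol article, mostly under Statistical analysis using YTO Models.

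- Each dependent variable is first corrected for age and sex with a model fitted in GNE controls. The stated aim is to separate normal ageing from what GE participants undergo through the disease.
- In the main GE models, "the potentially nonlinear influence of YTO is modeled using restricted cubic splines", with random effects for participant and family.
- For imaging against "clinical outcomes in GE individuals, we apply modeling techniques as described above". The content is then given: "The models include random effects of subject and family, but exclude age and sex", because the values have already been corrected. The splines in this paragraph are placed on the relation between biomarker and clinical measure.
- Direction and reading: "Imaging measures are generally predictor variables, and clinical measures are the outcomes, reflecting the potential causal relationships between the two measurement classes".
- YTO enters only through an additional step: "we also split our GE participants into two groups with a cutoff of 20 YTO and test for differences in the imaging versus clinical relationships".
- For all analyses a p "value of < 0.05 is considered statistically significant".

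Under Power analysis and sample size calculation, the central hypothesis is that "GE individuals will demonstrate significantly larger brain volume (primary outcome measure) and stronger cognition scores (secondary outcome measures) prior to 20 YTO", with the reverse for both between 20 and 0 YTO.

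**The concern.** The reason for leaving out age and sex does not extend to YTO. The GNE correction takes out what age does in people without the expansion. What the disease does along YTO stays in the imaging measure and in the clinical measure, by design. YTO is calculated only from age and CAG length, neither of which brain volume can cause. It is therefore an upstream common cause of both sides of the regression, not a mediator that adjustment would wrongly remove. If both sides follow YTO, they correlate even when the brain measure has no bearing on the clinical one.

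The comparison across 20 YTO can suffer in the same way. If both measures are flat above 20 YTO and fall below it, the slope of one on the other differs between the two groups through YTO alone.

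These models serve the second listed objective (brain structure against cognitive, behavioural and neurologic assessments), and the text attaches a potential causal reading to them. As written they cannot separate brain change that explains clinical change from two measures that both track time to onset.

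**Working it through.** **The plan's own figures.** The article gives no power or error rate for the imaging-clinical models. Table 5 concerns the YTO effect on each measure, and it reproduces. For the General Ability Index (GAI): 13.50 × 180/79 = 30.76 (printed 30.78). With ddf scaled to 87.66 × 2.278 = 199.7, NCP = 30.753 − 2 × 30.753/199.7 − 1 = 29.445, as printed. So its F values can be used to size the shared YTO signal.

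**Share of variance carried by YTO.** Approximate partial R² = ndf × F / (ndf × F + ddf), Kids-HD columns of Table 5:

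- GAI: 13.50/(13.50 + 87.66) = 0.133
- PANESS: 8.92/(8.92 + 46.12) = 0.162
- Cortical gray matter: 12.22/(12.22 + 99.90) = 0.109
- Whole brain: 23.37/(23.37 + 62.63) = 0.272
- Striatum: 69.90/(69.90 + 102.37) = 0.406

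**Induced correlation with no direct link.** The largest value is ρ = √(R² imaging × R² clinical), reached only if the two YTO curves have the same shape. The two-sided 5% rejection rate by Fisher z with n = 180 is approximately Φ(atanh(ρ) × √177 − 1.96):

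| Pair | ρ | Rate |
|---|---|---|
| Cortical gray matter, GAI | 0.121 | 36% |
| Whole brain, GAI | 0.190 | 73% |
| Striatum, GAI | 0.233 | 88% |
| Striatum, PANESS | 0.256 | 94% |

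Kids-HD effects may be optimistic. Halving both R² values halves ρ: whole brain with GAI falls to 0.095 (25%), and striatum with PANESS to 0.128 (40%).

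**Simulation.** Setting: 180 GE participants, about 400 visits, random-intercept maximum likelihood, no imaging-clinical link given YTO. Assumptions not in the article: CAG mean 44 and SD 2.8 within 40-56, ages 6-30, intraclass correlation 0.95 for imaging and 0.80 for clinical measures, and an exponential onset curve, 21.54 + exp(9.556 − 0.146 × CAG). That form reproduces the Introduction's example of 26 YTO (48.1 − 22 and 34.3 − 8); the formula as printed does not. Curves were both linear in YTO, both hinged at 20 YTO, or one of each.

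| Test | No YTO term |
|---|---|
| Cortical gray matter, GAI | 16-35% |
| Whole brain, GAI | 36-73% |
| Striatum pairs | 50-94% |
| 20-YTO slope difference, both linear | 5-7% |
| 20-YTO slope difference, one linear and one hinged | 12-16% |
| 20-YTO slope difference, both hinged | 32-60% |

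The low end of each range for the main association comes from unlike shapes, the high end from matching ones. With a YTO spline added, rates are about 2-8%. Repeat runs of the slope-difference test gave 6-9%, 16-21% and 31-66% for the three shape settings, so these figures are orders of magnitude.

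**The case against.** **The omission is inferred.** The sentence excludes age and sex, not YTO; the models are said to follow the techniques already described; and the article is condensed. This only partly stands. The paragraph lists what the models contain, gives a reason for what is left out, and puts the splines on the biomarker. Anyone following it would fit no YTO term.

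**An unadjusted association is a legitimate descriptive target, and the causal phrase mainly explains which variable is predictor.** This stands as far as it goes. It supports keeping the unadjusted result as description, not reading it as a relation beyond shared stage.

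**The size depends on the pair and on curve shape.** This stands. A reader might infer that most null associations would be declared significant, at something like 70-93%. The documents do not support that as a general statement. Such rates need whole-brain or striatal measures whose curve matches the clinical one. Table 5 itself gives different degrees of freedom (1 for GAI and PANESS, 3 for whole brain, 5 for striatum), and the Introduction describes striatal volume as close to controls until 20 YTO and falling thereafter. Cortical gray matter, marked as a primary outcome, stays at about 16-35% with GAI. GAI and PANESS are marked as secondary outcomes in Table 5 but are not in the Table 6 battery, so the rates for the tests actually administered are unknown.

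**Strong inflation of the 20-YTO comparison needs both measures to be flat above 20 YTO.** This stands too. The central hypothesis has GE brain volume and cognition above GNE there, which is not flat at the control level.

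**Adjustment is not a complete cure.** The near-nominal simulated rates arise because calculated YTO was made the true common cause. The article says true time to onset is distributed around the CAG-specific mean, so some confounding by true stage would remain.

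**Conclusion.** The concern holds. The stated models omit YTO, the GNE correction leaves the YTO trend on both sides, and the protocol expects both sides to follow it. Shared disease stage can therefore yield a significant imaging-clinical association far more often than 5%: roughly 15-95% across the pairs examined. The 20-YTO difference test is badly affected only if both measures change mainly below 20 YTO.

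These sizes rest on R² values approximated from Kids-HD F statistics, 180 participants and 400 visits, and assumed intraclass correlations, CAG distribution and curve shapes. The GE sample in these models may be below 180, because repeats of 36-39 and above 70 are set aside from the YTO analysis. The direction of the problem does not depend on these choices as long as both measures follow YTO with related shapes.

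This should be fixed, but it does not threaten the study's main result: the tests of the central hypothesis model YTO directly and are untouched. It is a cheap improvement.

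**What to change.** In the imaging-clinical paragraph of Statistical analysis using YTO Models:

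1. Add the restricted cubic spline in YTO already used in the main GE models (or age and CAG length) as a covariate in every GE imaging-clinical model, including those that "split our GE participants into two groups with a cutoff of 20 YTO and test for differences in the imaging versus clinical relationships".
2. Base any statement that an imaging measure relates to a clinical measure, and any causal reading, on the YTO-adjusted coefficient.
3. Report the unadjusted association only as a description of joint change along YTO.
4. Note that calculated YTO leaves some residual confounding by true disease stage.

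The cost is a few sentences and a few model degrees of freedom, with no new data; collection is still under way, so the change can precede analysis. The adjusted associations will be weaker and slightly less precise.

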### The ChANGE-Juvenile Onset HD (ChANGE-JOHD) Study

As part of the same study and funding mechanism, we are also conducting the “ChANGE-Juvenile Onset HD (ChANGE-JOHD) Study,” which will leverage the same infrastructure and multi-site design as the ChANGE-HD study. Although most HD patients typically manifest obvious motor signs between the ages of 40 and 50 (known as Adult-Onset HD, AOHD), a much smaller percentage of patients are diagnosed with motor features before the age of 21 (classified as JOHD) [27]. Patients with JOHD experience the same triad of cognitive, behavioral, and motor symptoms as those with AOHD, albeit with distinct phenotypes [82]. Specifically, JOHD patients tend to exhibit less hyperkinesia and more hypokinesia compared to AOHD. However, patients with JOHD experience CAG repeat expansion and symptom progression at a faster rate compared to patients with AOHD [83]. The progression of JOHD is theorized to involve several neuropathologic mechanisms, including reduced gestational neurogenesis and cell differentiation, neuronal migration, and synaptogenesis, as well as hyper and hypo-synaptic pruning during puberty [84]. However, due to its rarity, many aspects of the neurobiology and progression of JOHD are unclear.

While large-scale observational studies of AOHD have significantly advanced our understanding of HD, JOHD patients have been largely excluded from these efforts [85]. As such, large-scale longitudinal studies in JOHD are needed to deepen our understanding of the pathophysiology, as well as therapeutic strategies. When the Kids-HD study began at the University of Iowa in 2009, children at risk for HD who were already manifesting motor signs were followed as well. This was called the Kids-JOHD study (which ran in parallel to the Kids-HD study), whose primary objective was to deepen our understanding of the course and progression of JOHD. Cross-sectional analyses showed that patients with JOHD have significant subcortical degeneration shortly after diagnosis, along with reduced general measures of growth (such as weight and BMI) compared to GNE controls [21,86,87]. Furthermore, the longitudinal trajectory of disease severity is markedly hastened and amplified in JOHD compared to AOHD [88]. Despite these initial assessments from the Kids-JOHD study, larger-scale longitudinal studies in JOHD are still lacking. To this end, we have developed the first ever multi-site, prospective and comprehensive study of JOHD, leveraging the established infrastructure of the titular ChANGE-HD study to record clinical and neuroimaging metrics in this population. This study, which is considered separate from the ChANGE-HD but also follows an ALD, aims to investigate whether comprehensive longitudinal quantitative assessments of motor skills, cognition, and neuroimaging in JOHD patients can yield reliable biomarkers of disease progression. A total of 40 patients with JOHD will be recruited. In the first year, 20 patients with JOHD (3–4 per site) will complete baseline assessments, with the remaining 20 patients undergoing baseline assessments in Year 2. Year 2 will also include annual follow-up visits for the first 20 patients. In Year 3, follow-up visits will be conducted for the second group of 20 patients. As of the time of this writing, we have collected 49 assessments from 34 participants. For the study, the comparator group will include GNE participants recruited in the ChANGE-HD protocol. Data and biospecimens collected from the ChANGE-JOHD study will be shared separately from the ChANGE-HD study after data collection and analysis of primary outcome measures are complete, which we estimate will occur in September of 2027. To participate, JOHD participants must:

Be diagnosed with JOHD by a trained neurologist prior to the age of 21, based on motor symptomology (the participant’s genetic status is confirmed after consent is obtained).Be between 6–30 years old at baseline. Thus, even though the diagnosis is made prior to 21, assessment for the study is not restricted to ages under 21.Not be bed-ridden, unable to communicate, or beyond travel conditions that are too strenuous for the individual.

## Discussion

ChANGE-HD is a longitudinal study designed to prospectively examine the neurodevelopmental phase of HD in premanifest at-risk children and young adults. The parallel ChANGE-JOHD study will also leverage the infrastructure of the ChANGE-HD study to investigate potential biomarkers of disease progression. Recruitment is currently underway at all six clinical sites. The data collected will provide crucial insights into the effects of *mHTT* and help uncouple neurodevelopmental changes from neurodegeneration.

Although recruitment is still ongoing, there are some prospects of how the results of ChANGE-HD may support the neurodevelopmental theory of HD. One such way is through antagonistic pleiotropy, as investigated by Neema et al. (2024) using the neuroimaging data of Kids-HD [17]. Therein, cortical hypertrophy and cognitive advantage were identified in the GE cohort very far from motor onset. If similar results are identified with the broader sample of ChANGE-HD, this would provide further support for the theory that *mHTT* confers developmental advantages antecedent to the degenerative phase.

Linked to this proposal is the theory of glutamatergic excitotoxicity in HD. It is a well-established fact that many neurological disorders are grounded in excessive neurotransmission through glutamatergic pathways which can then cause the development of epilepsy and/or cortical and subcortical volumetric atrophy [89–92]. Cortico-striatal pathways, which are highly implicated in the pathogenesis of HD, are primarily glutamatergic in nature [93]. If cortical hypertrophy is indeed characteristic of the developmental phase of HD, it is possible that a concomitant increase in glutamatergic neurotransmission is present as well. If this is true, there may be a direct causal link between developmental hypertrophy and downstream atrophy of striatal volume. Although neurochemical data, which we are not collecting, will be needed to confirm this hypothesis, the ChANGE-HD study is designed to test several assumptions of the glutamatergic toxicity model through our collection of high-quality longitudinal neuroimaging (structural and functional) data. For example, we will determine whether abnormalities in corticostriatal resting state functional connectivity and white matter integrity can be observed during the neurodevelopmental, as well as neurodegenerative, phases of the disease.

Like other HD studies, the ultimate goal of the ChANGE-HD study is to guide the design of interventions to prevent or mitigate HD symptoms. Reproducing the findings of early-life advantages in GE individuals observed in the Kids-HD sample [17] would bolster support for the antagonistic pleiotropy theory of HD and caution against mutant Huntington downregulation early in the disease process. Indeed, if the gene confers a benefit, then such treatments may come at a cost before neurodegeneration has begun. We also expect that studying the disease before brain function decline will reveal new neuroimaging patterns that predict neurodegeneration. For example, outlining the time course of motor and frontal resting state functional connectivity patterns may reveal when corticostriatal hypertransmission begins to negatively affect behavior. Pharmaceuticals to alter glutamatergic concentrations associated with these connectivity patterns may be a promising line for therapeutics. Finally, we will investigate how genetic modifiers (i.e., *FAN1*, *MLH1*, *PMS1*, etc.) affect the trajectory of the disease process before neurodegeneration begins. While these modifiers are related to the continued expansion of CAG repeats (somatic expansion) and well-studied later in the disease process, it is unclear how they contribute to neurodevelopment. Linking these modifiers to neurodevelopment may reveal important neuropathological insights or uncover new interventional targets.

